**Sample size calculation**

Assuming that the prevalence of symptomatic RTIs is 30% in the controls and the prevalence of laboratory-proven respiratory viral infection in controls is approximately 12% the intervention could be considered clinically worthwhile if it can reduce the prevalence of syndromic or proven viral RTI by 50%.21,22

Assuming a moderate intra-cluster correlation of 10% and a mean of 75 participants per cluster (tent), and inflating the sample by a factor of 8.4 to account for clustering, the sample size required for a cRCT to detect a reduction from 12% to 6% with 80% power at 5% significance is 2976 per arm. An additional inflation factor of 1.18 will allow for up to 15% loss to follow-up or incomplete outcome data. This results in a sample size of approximately 3500 participants per treatment making a total of 7000.

For the first primary outcome (clinical/syndromic RTIs) a smaller sample would be sufficient to answer a more generic question, namely prevention of symptomatic RTI. The sample size required for detecting a reduction from 30% prevalence of RTIs to 15% with 80% power at 5% significance and considering for clustering and loss to follow-up is about 1170 participants per treatment making a total of 2340.

| **Countries** | **Total number of pilgrims** | **Number of recruits** | |
| --- | --- | --- | --- |
| **2013** | **2014** |
| Saudi Arabia | 1,000,000 | 2,200 | 2,200 |
| Indonesia | 200,000 |  | 500 |
| India | 170,000 |  | 450 |
| Pakistan | 150,000 |  | 350 |
| Turkey | 120,000 |  | 300 |
| Bangladesh | 65,000 |  | 200 |
| Morocco | 32,000 |  | 100 |
| Malaysia | 28,000 |  | 100 |
| Australia | 5,000 | 200 | 200 |
| Qatar | 2,000 | 100 | 100 |
| Total | 1,770,000 | 2500 | 4500 |

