**Specimen collection and testing**

In both groups of tents the study team members will actively search for pilgrims suffering from ILI (defined as subjective or measured fever and at least one respiratory symptom such as cough, sore throat and rhinorrhea) at least once every day. A study team member will collect nasopharyngeal (NP) swab (or throat swab if an NP swab is not doable) for molecular diagnostic testing for respiratory viruses. As a part of the routine care pilgrims in both tent groups will be supplied with generic medications (such as acetaminophen and ibuprofen) for fever or aches in addition to antiviral drugs for confirmed influenza patients.

The swabs will be stored within 2-3 hours at subzero temperature for later molecular diagnostic testing at the Centre for Infectious Diseases and Microbiology Laboratory Services (CIDMLS), Westmead Hospital, NSW, Australia. Pilgrims will provide their email addresses, phone numbers and mail addresses if they wish to receive the results of the laboratory test. Multiplex reverse transcriptase polymerase chain reaction (RT-PCR) for influenza A and B, MRES CoV and other corona viruses, parainfluenza viruses (types 1,2, 3 and 4), RSV A and B, adenoviruses, human metapneumovirus (hMPV), and picorna viruses will be performed. Nasal swabs will be taken for reverse transcriptase polymerase chain reaction (RT-PCR) analysis of respiratory virus infection. The swab used will be Copan nylon flocked dry nasal swab. The study staff who will take the swab will all have been trained to achieve an appropriate sample.

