**Data analysis**

Data available from questionnaires, diaries and laboratory tests will be analysed anonymously to examine whether mask use makes a significant difference in reducing the frequency of laboratory-confirmed respiratory virus infection (including influenza, corona virus or other respiratory viruses). The primary endpoints (effectiveness and efficacy of facemasks against ILI and laboratory-confirmed viruses respectively) will be analysed by intention to treat.

The self-reported uptake rates of influenza vaccination will be determined and vaccine effectiveness will be estimated based on the case-negative case-control methodology.

The results from the genomic sequencing of influenza virus will assist us understanding the genetic relatedness of circulating influenza strains at Hajj and the transmission pattern of influenza among pilgrims.

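### The syndromic primary outcome is sized as symptomatic RTI but analysed as febrile ILI, so the stated power with the 2013 sample does not belong to it; the swab trigger and the basis of the 12% laboratory rate also need to be fixed

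*Protocol*

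**What the plan says.** **Sizing (Protocol, Sample size calculation).** The planning assumption is that "the prevalence of symptomatic RTIs is 30% in the controls and the prevalence of laboratory-proven respiratory viral infection in controls is approximately 12"%. The target is to "reduce the prevalence of syndromic or proven viral RTI by 50"%, that is, 30% to 15% and 12% to 6%. The section calls the first primary outcome clinical or syndromic RTI. It gives about 1170 per arm (2340 in all) for that outcome and about 3500 per arm (7000 in all) for laboratory-proven infection. The text after Table 1 adds that the 2013 recruits, about 2500 and at least 2340, will settle the RTI outcome, and that the 2014 recruits complete the laboratory outcome.

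**Analysis (Protocol, Data analysis).** The primary endpoints are given as "effectiveness and efficacy of facemasks against ILI and laboratory-confirmed viruses respectively".

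**Case definition and swabbing (Protocol, Specimen collection and testing).** Staff look daily for ILI, "defined as subjective or measured fever and at least one respiratory symptom such as cough, sore throat and rhinorrhea", and the next sentence has them collect a swab. Figure 2, under Recruitment, says only that pilgrims with symptoms are swabbed and does not mention fever. Under Data collection, participants record respiratory symptoms and fever in the diary each day.

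Symptomatic RTI is not defined, and no ILI rate is given.

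**The concern.** The first primary outcome has one name where it is sized and another where it is analysed, and the second is narrower. ILI needs fever as well as a respiratory symptom. On the ordinary reading of symptomatic RTI, every ILI case is an RTI case but not the reverse. The ILI rate in controls can then be at most 30%, and it is lower if some RTIs are afebrile. With the relative reduction held at 50%, a lower control rate means a smaller absolute difference and less power.

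The claim most exposed is that the 2013 sample will answer this outcome, because 2340 leaves no margin above 80% power even at a 30% rate.

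The laboratory endpoint has a related gap. If a swab is taken only when ILI is found, laboratory-confirmed cases are ILI cases with a positive swab and cannot outnumber ILI cases. The protocol does not say whether the 12% was meant on that basis. Laboratory-confirmed infection is the stated primary aim and determines the 7000, and an infection not swabbed at Mina cannot be recovered later.

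**Working it through.** **Inputs, all from Sample size calculation.** Control rates 30% and 12%; 50% reduction; 80% power; 5% significance (two-sided reproduces the figures); "Assuming a moderate intra-cluster correlation of 10% and a mean of 75 participants per cluster (tent"); "inflating the sample by a factor of 8.4 to account for clustering"; a further factor of 1.18 for up to 15% loss.

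**Step 1: reproduce the plan.** Design effect = 1 + (75 − 1) × 0.10 = 8.4. The per-arm size before clustering is n = (1.960 + 0.842)² × [p₁(1 − p₁) + p₂(1 − p₂)] / (p₁ − p₂)².

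- 12% to 6%: 7.849 × 0.1620 / 0.06² = 353.2, rounded up to 354. Then 354 × 8.4 = 2974 (stated 2976), and × 1.18 = 3509 (stated about 3500).
- 30% to 15%: 7.849 × 0.3375 / 0.15² = 117.7, rounded up to 118. Then 118 × 8.4 × 1.18 = 1170 (stated about 1170).

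The arithmetic is sound. Only the match between rates and endpoints is in question.

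**Step 2: effective sizes.** After loss and clustering, 1170 per arm becomes 1170 / 1.18 / 8.4 = 118.0, and about 3500 per arm becomes 2976 / 8.4 = 354.3.

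**Step 3: power for ILI at lower control rates.** Power = Φ(|p₁ − p₂| / √{[p₁(1 − p₁) + p₂(1 − p₂)] / n} − 1.960). The ILI rates below 30% are assumptions, since the protocol gives none. The 50% reduction and the 0.10 correlation are kept.

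Example, 20% to 10% with n = 118.0: standard error = √(0.2500 / 118.0) = 0.0460; 0.10 / 0.0460 = 2.17; Φ(2.17 − 1.96) = 58%.

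| Control ILI rate | Power, 2340 in all | Power, 7000 in all |
|---|---|---|
| 30% (as planned for RTI) | 80% | 99.8% |
| 20% | 58% | 96% |
| 15% | 45% | 89% |
| 12% | 37% | 80% |
| 10% | 31% | 72% |

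With 2500 rather than 2340 in 2013, the powers at 20%, 15% and 10% are 61%, 48% and 33%. A pooled-variance formula changes the tabulated values by about one percentage point or less.

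**Step 4: laboratory endpoint, conditional.** Suppose that only febrile cases are swabbed, that the 12% includes afebrile infections, and that the febrile share among proven infections is the same as in Step 3 (20/30 or 15/30). The control rate becomes 12% × 20/30 = 8%, or 12% × 15/30 = 6%. With n = 354.3:

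- 8% to 4%: standard error = √(0.1120 / 354.3) = 0.01778; 0.04 / 0.01778 = 2.25; power 61%.
- 6% to 3%: standard error = √(0.0855 / 354.3) = 0.01553; 0.03 / 0.01553 = 1.93; power 49%.

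If instead the 12% already counts only febrile, swabbed cases, power stays at 80%.

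**The case against.** **The two names may mean one event.** Symptomatic RTI is undefined, the protocol moves between RTI and ILI for the same outcome, and its ILI definition is broad (subjective fever counts, with any one respiratory symptom). The 30% could be a loosely worded ILI rate. That is possible, but the protocol does not say so, and the sizing section itself calls symptomatic RTI the more generic question. The mismatch therefore stands until the text settles it.

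**The full trial protects the ILI comparison.** This stands. With all 7000, ILI keeps about 80% power down to a control rate of about 12%. A reader might infer that a null ILI result would be uninformative; at 20% or 15% with the full sample that is not so. The exposed claim is the one about 2013 alone.

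**The laboratory loss is not shown.** This also stands. The sizing and analysis sections use equivalent names for that endpoint, and the protocol does not say whether the 12% counts all infections, those with any symptom, or only febrile ones. Carrying the febrile share over to proven infections is equivalent to holding swab positivity at 12/30 = 40%, a ratio of two planning rates and not a documented figure. If febrile cases are positive more often, the laboratory rate falls less.

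**Afebrile cases may be swabbed.** A reader might infer from Specimen collection and testing that the trial counts and swabs febrile ILI only. The documents do not support so flat a statement: Figure 2 has no fever condition, the diaries capture respiratory symptoms separately from fever, and nothing forbids swabbing an afebrile case. What remains is an inconsistency about who is swabbed for a primary endpoint.

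**Conclusion.** The point holds for the syndromic outcome and, conditionally, for the laboratory outcome.

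- **Syndromic.** The 80% power at 2340 and the claim for 2013 belong to a 30% symptomatic-RTI rate, not to ILI as defined, if any RTI is afebrile. The size of the loss depends on an ILI rate that the protocol does not give. Over an assumed 20% to 10%, power is about 58% to 31% with 2340 and about 96% to 72% with 7000.
- **Laboratory.** Power at 7000 is below 80% only if swabbing is confined to febrile cases and the 12% includes afebrile infections; 61% and 49% are illustrations at control rates of 8% and 6%. It would go too far to say that both stated powers are wrong, or that both control rates will certainly be lower than planned.
- **Swab trigger.** Figure 2 and Specimen collection and testing differ on who is swabbed, whatever the rates turn out to be.

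Sample size, case definition and swab trigger are matters for the protocol, since they govern recruitment and what is collected at Mina.

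**What to change.** Use one case definition for sizing, swab trigger and syndromic endpoint. There are two ways to do this:

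1. **Keep ILI.** Replace the 30% and 12% by control rates for ILI and for ILI with a positive swab. Tabulate the power that 2340 and 7000 give over a range of ILI rates, such as 10% to 30%. Limit the statement about 2013 to the rates at which it holds.
2. **Keep symptomatic RTI.** Define it, and make it the syndromic primary endpoint in Data analysis. The diaries already record the symptoms needed.

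In both cases, reconcile Figure 2 with Specimen collection and testing on who is swabbed, with the same rule in both arms, and state which cases the 12% counts. If it already means febrile, swabbed cases, one sentence settles that part.

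**Cost.** The first option is a change of wording with a less favourable stated power. The second needs no new diary data. If afebrile cases are also to be swabbed, it needs more swabs of the same kind: at the planned rates at most about 0.30 × 3500 + 0.15 × 3500 = 1050 + 525 = 1575 swabs in total, including those already planned for febrile cases.

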**Table 1: Proposed number of pilgrims from each participating country**

To achieve the full sample size we aim to conduct the study over two years (2013 and 2014). About 2500 pilgrims (or at least 2340) will be recruited in 2013 which will give an answer for the RTI outcome and could build on that sample for the second outcome (proven infection) which ultimately will be completed by recruiting another 4500 pilgrims in 2014. Proportionate (or balanced) number of pilgrims will be recruited from each participating country according to the number of pilgrims attending Hajj from these countries (see Table 1).

**Ethics implication**

We got ethics approval to conduct a pilot study involving Australian pilgrims until December 2013 (reference: 11/SCHN/162). We also obtained a Saudi Arabian ethics approval for the pilot trial (reference: KACST: H-01-R-012), and a fresh application is being made for this main trial. Ethics approval is being sought from the Joint Institutional Review Board (J-IRB) of Hamad Medical Corporation - Weill Cornell Medical College in Qatar. The study coordinator will provide a modified ethics committee submission for collaborators and assist them to apply for ethical approval from the relevant Ethics Committees. Only participants who provide written informed consent to take part will be included in the study. Participants will be told that taking part in this study would be voluntary and confidential. All participants will be assigned a study identification (ID) number. Data will be collected and stored under this number only, so that all data are stored anonymously by study ID number only. Hard copies of the questionnaires will be stored securely in a locked filing cabinet in locked offices and electronic data will be stored in password-protected computer files. Only members of the research team will have access to the data. The hard copies will be retained for at least fifteen years (or more, if the data management protocol of the participating country requires so) and will be disposed according to standard data management guidelines.

